### Data Collection

Clinical information of all enrolled patients will be retrieved from the hospital electronic or paper records system, including the following:

Baseline demographic dataDays of illness durationPresenting symptomsRadiological findings (chest x-ray and computed tomography [CT] scan chest, if possible) on the day of hospital admission; on the day of ICU admission; on the day of CP infusion (day 0); and on days 3, 7, 14, and 30Laboratory infectious marker testing results like respiratory, urinary, or blood cultureLaboratory inflammatory markers: CRP (day of CP infusion [day 0] and then on days 3, 7, 14, and 30)Application of assisted mechanical ventilation and their modes, intranasal oxygen inhalation, number of days of intubation, or nasal oxygen supportMedication regimen (eg, hydroxychloroquine, azithromycin, any antiviral therapies, steroids, tocilizumab)Complications including acute renal failure, acute coronary syndrome, myocarditis, ARDS, gastrointestinal complication, and nosocomial infectionThe SARS-CoV-2 RNA from the serum sample will be monitored during treatment and at day 14 of recovery or discharge, whichever is later.

We plan to test for all of the following parameters for patients with COVID-19:

Complete blood count (CBC) differential to include percent and ALC, and percent and absolute neutrophil countChemistry panel to include total protein, albumin, lactate dehydrogenase, alanine aminotransferase and aspartate aminotransferase, and procalcitoninCardiac biomarkers (eg, cardiac troponins)Creatine phosphokinaseFerritinFull coagulation profile to include partial thromboplastin (PT), activated PT time, fibrinogen, and D-dimerCRPOxygen saturationRadiological examinationABO RhD grouping and antibody screeningrRT-PCR test for SARS-CoV-2Test for IgG and IgM antibodies against SARS-CoV-2

CP donors will essentially undergo routine blood donation processes such as donor history questionnaire, clinical examination, and testing for the infectious marker (serology and nucleic acid testing methods) along with ABO RhD grouping, antibody screening, and CBC. They will also undergo a test for IgG and IgM antibodies against SARS-CoV-2, which should be positive for IgG.

Data collection forms have been developed to collect data for CP donors, recipients, and controls (comparators).

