### Study Endpoint and Outcome Measures

Our primary endpoints are ICU (or designated area for critical patients) length of stay; safety of CP; and reporting of SAE such as anaphylaxis, TRALI, and TACO.

Our secondary endpoints will include number of days on mechanical ventilation, 30-day mortality, and days to clinical recovery as defined by the MOH.

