### Study Population

A total sample size of 575 patients, 115 CP recipients and 460 matched controls (1:4 ratio), will be sufficient to detect a clinically important difference of 11.6% between two groups (CP recipients vs matched controls) in 30-day mortality using a two-tailed *z* test of proportions and chi-square test with 80% power and a 5% level of significance. This 11.6% difference represents a 12.4% mortality in the CP recipient group and 24.4% mortality in the matched control patients [23].

The treatment group (CP recipients group) will have 115 patients who have COVID-19 but have not recovered yet as per the inclusion criteria. The control group (comparator group) will have 460 patients who are either not consenting to receive CP or those who will not be able to receive CP due to nonavailability to compare the efficacy of the CP. Control group patients will be subjected to propensity score (PS) matching based on age, gender, diabetes mellitus (DM), hypertension (HTN), and intubation.

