### Statistical Analysis

Descriptive and inferential statistics will be used to characterize the study sample and test the hypotheses. Descriptive results for all quantitative variables such as age will be presented as mean (SD; for normally distributed data) or median with interquartile range (for data not normally distributed), while numbers (percentage) will be reported for all qualitative variables such as gender.

To assess the independent effect of CP transfusion safety and survival, we will conduct a PS-matching (based on age, gender, DM, HTN, and intubation) analysis. Among the predictors, exact matching will be enforced to achieve the balance for all predictors between the plasma and control groups.

The bivariate analysis will be performed using independent sample *t* test, Mann-Whitney *U* test, Pearson chi-square test, or Fisher exact test whenever appropriate to compare the demographic characteristics (eg, age, gender, nationality) and clinical characteristics (improvement in oxygenation, laboratory parameters, radiological findings, complications, and length of hospital stay) between those who will receive the CP and those who will not receive this therapy.

The multiple binary logistic regression model will be used to assess the effect of CP transfusion on 30-day mortality after adjusting for potential confounding factors compared to matched controls patients. The adjusted odds ratio and 95% confidence interval for the adjusted odds ratio will be reported. The Hosmer-Lemeshow goodness-of-fit statistics will be used to determine whether the model adequately describes the data.

The time-to-event analysis will be measured from the date of diagnosis. The overall survival at 30 days and 3 months will be evaluated using the Kaplan-Meier estimator and compared between the two groups (plasma recipients vs matched control patients) using the log-rank test. A Cox proportional hazard model will also be used to estimate the hazard ratio for in-hospital 30-day mortality for the plasma group compared with matched control group patients after adjusting for potential confounding factors. In addition, interactions between CP administration and all the predictors will be tested to see if the plasma effects will be the same in subgroups. A *P*<.05 (two-tailed) will be considered statistically significant. All statistical analyses will be performed using SPSS version 24 (IBM Corp).

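### Primary ICU length of stay has no start day common to both groups, so any wait for plasma selects recipients with longer stays and biases the comparison against plasma

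*Protocol article*

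**What the plan says.** The Protocol article (Study Endpoint and Outcome Measures) gives one primary efficacy endpoint; the other primary items concern safety: "Our primary endpoints are ICU (or designated area for critical patients) length of stay". Ventilation is handled in the same form: "Our secondary endpoints will include number of days on mechanical ventilation". Neither endpoint has a start day.

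Inclusion Criteria and Exclusion Criteria make the need for ICU care part of entry. Data Collection schedules imaging "on the day of ICU admission; on the day of CP infusion (day 0"), so ICU admission and infusion are foreseen as separate days. Controls are given no day 0.

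Study Population says that the treatment group "will have 115 patients who have COVID-19 but have not recovered yet as per the inclusion criteria". Controls are patients who do not consent or "those who will not be able to receive CP due to nonavailability". Controls undergo "propensity score (PS) matching based on age, gender, diabetes mellitus (DM), hypertension (HTN), and intubation".

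Statistical Analysis repeats these five variables and compares length of hospital stay by ordinary two-group tests, according to whether plasma was received. The only time origin stated is for survival: "The time-to-event analysis will be measured from the date of diagnosis".

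**The concern.** Group membership is settled after the clock for the outcome has started. A patient who leaves ICU quickly has little chance to be infused, while a patient who stays long has more. If a unit comes too late, the patient fits the control definition and brings a short stay with them. Days in ICU before infusion, which plasma cannot influence, are counted in the recipients' outcome. This is length-selection (immortal-time) bias.

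Matching on intubation does not remove it, because that records a state and not the days already spent in ICU or on the ventilator. At stake is the only primary efficacy comparison: a real shortening of stay could be diluted, cancelled or reversed. A larger sample would only make the biased answer more precise.

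**Working it through.** **Plan's own figure.** There is none for ICU stay. The 115 + 460 = 575 patients are sized on 30-day mortality and do not bear on this point.

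**Inputs from the article.** Recipients are not yet recovered at infusion; controls are everyone else (refusal or nonavailability); time in ICU is not matched.

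**Inputs assumed, because the article does not give them.** ICU stay L has mean m = 10 or 14 days, exponential or gamma with shape 2. The wait W from ICU entry to plasma is exponential with mean w = 1, 3 or 5 days, independent of L. A share l = 30% is listed (consents and could be offered plasma). There are no deaths and no plasma effect. A listed patient with W < L becomes a recipient; all others are controls.

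**Formulas.** Let P = Pr(W < L), p = l·P, and R = recipients' mean total stay. The controls' mean is C = (m − pR)/(1 − p), so

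excess = R − C = (R − m)/(1 − p).

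Against unlisted patients alone (refusers), the excess is R − m.

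- Exponential stay: P = m/(m + w) and R = m + mw/(m + w).
- Gamma stay, shape 2, with b = 2/m and a = 1/w: P = 1 − [b/(a + b)]² and R = [m − 2b²/(a + b)³]/P.

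**Worked case** (exponential, m = 10, w = 3). P = 10/13 = 0.769 and p = 0.3 × 0.769 = 0.231. R = 10 + 30/13 = 12.31. C = (10 − 0.231 × 12.31)/0.769 = 9.31. The excess is 3.00 days; against refusers alone it is 2.31.

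**Results (days, true effect zero)**

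| Stay | m | w | Recipients | Controls | Excess | Excess vs refusers |
|---|---|---|---|---|---|---|
| Exponential | 10 | 1 | 10.91 | 9.66 | 1.25 | 0.91 |
| Exponential | 10 | 3 | 12.31 | 9.31 | 3.00 | 2.31 |
| Exponential | 10 | 5 | 13.33 | 9.17 | 4.17 | 3.33 |
| Exponential | 14 | 1 | 14.93 | 13.64 | 1.30 | 0.93 |
| Exponential | 14 | 3 | 16.47 | 13.19 | 3.28 | 2.47 |
| Exponential | 14 | 5 | 17.68 | 12.95 | 4.73 | 3.68 |
| Gamma 2 | 10 | 1 | 10.24 | 9.90 | 0.34 | 0.24 |
| Gamma 2 | 10 | 3 | 11.02 | 9.64 | 1.38 | 1.02 |
| Gamma 2 | 10 | 5 | 11.67 | 9.52 | 2.15 | 1.67 |
| Gamma 2 | 14 | 1 | 14.19 | 13.92 | 0.28 | 0.19 |
| Gamma 2 | 14 | 3 | 14.97 | 13.64 | 1.33 | 0.97 |
| Gamma 2 | 14 | 5 | 15.72 | 13.43 | 2.28 | 1.72 |

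With w = 0, R = m and the excess is 0. Simulation agrees with these values to within 0.1 day. A wider grid (m = 8 or 12, 20% to 80% refusing, w = 1 to 5) gives an excess of 0.3 to 8.1 days.

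**Which correction works.** Null differences were simulated under each rule.

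- Moving only the recipients' clock to infusion: −1.6 to +4.6 days on the wider grid. Not a cure.
- Same index day, controls still in ICU but drawn only from patients never treated: recipients still longer by about 0.1 to 0.7 days with 30% listed, and 0.5 to 3.7 days with 80% listed. Excluding patients infused later removes long stayers from the controls.
- Same index day, controls still in ICU and not yet treated on that day: zero within simulation error (at most about 0.05 day). This also follows directly: if W is independent of L, the remaining stay given L > t is the same whether W = t or W > t.

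**The case against.** The article does not say in words that ICU days before infusion count, nor that a patient who leaves ICU while waiting becomes a control. Nonavailability could be settled at entry, for example where no compatible unit exists. Deriving a length-of-stay variable is often left to the full protocol or analysis plan, and Data Collection does label infusion as day 0. Plasma may be stored frozen for up to a year, so waits could be short. Non-randomisation is openly listed as a limitation.

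Much of this stands as a limit on size. It does not remove the point. The control definition and the matching variables are fixed in this article, and together with a stay endpoint they create the selection. A day-0 clock for recipients alone does not repair it, since controls have no day 0. Nor does the bias depend on reading nonavailability broadly: against refusers alone it is still 0.2 to 3.7 days in the table above.

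Three stronger readings are tempting and not supported:

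- That recipients will show a longer stay whatever happens. This needs a wait, and the article gives no waiting time. Confounding by severity could add to or offset the bias.
- That the 40-patient interim would fail for this reason. Time of the Study speaks only of showing benefit, and Interim Analysis only of a similar analysis; neither ties the decision to ICU stay.
- That every outcome is biased against plasma. For survival counted from diagnosis, the same guaranteed time would favour plasma; that is a separate matter.

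**Conclusion.** The point holds in conditional form. As written, the primary ICU-stay comparison, and with it ventilator days, is biased against plasma whenever infusion follows ICU entry after a delay. Under the stated assumptions (mean stay 10 to 14 days, 30% listed, independent exponential wait, no deaths, no effect), the excess in mean stay is zero with no wait, 0.3 to 1.3 days with a 1-day mean wait and 1.3 to 4.7 days with a 3- to 5-day mean wait. The direction of this mechanism is clear; its size in this trial cannot be known from the article. Deaths were not modelled: patients who die in ICU before plasma arrives would also enter the controls with short stays. This should be fixed. It is not shown to be fatal, because the wait may be short.

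**What to change.** Define the endpoint as ICU days, and as secondary ventilator days, from a common index day to day 30.

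- **Recipients:** the index day is the first infusion.
- **Controls:** each must be still in ICU and not yet given plasma after the same number of ICU days as its matched recipient had at infusion, and is counted from that day. A patient infused later may serve as a control until then. State how follow-up is handled at that infusion, for example by censoring.
- **Death:** state how it is scored, so that an early death does not count as a short stay. One option is ICU-free days to day 30 with death scored as zero. The rule for controls infused later must be compatible with the measure chosen.
- **Data:** record ICU discharge dates; Data Collection lists the ICU admission and infusion days but no discharge date.
- **Total ICU stay:** show it descriptively only.

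The cost is revised protocol wording, one more date on the form and somewhat more complex matching. There will be fewer usable controls for recipients infused late, which may make the 1:4 ratio harder to reach for them.

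### ICU stay and ventilator days are raw day counts that death cuts short, so the only non-safety primary endpoint can move against a survival benefit, to a degree set by when deaths occur

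*Protocol article*

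**What the plan says.** All places are in the Methods of the protocol article.

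- *Study Endpoint and Outcome Measures*, primary: "Our primary endpoints are ICU (or designated area for critical patients) length of stay", followed by plasma safety and the reporting of serious adverse events. ICU stay is the only one of these that is not a safety item, although the text does not itself use the label efficacy.
- Same section, secondary: "number of days on mechanical ventilation, 30-day mortality, and days to clinical recovery as defined by the MOH". Ventilation is a count of days, and mortality is a separate endpoint.
- *Study Population* plans for "12.4% mortality in the CP recipient group and 24.4% mortality in the matched control patients", with 115 recipients and 460 matched controls. No effect size is given there for ICU stay.
- *Statistical Analysis* names the t test, Mann-Whitney, chi-square and Fisher tests for a list of characteristics that ends with "complications, and length of hospital stay) between those who will receive the CP and those who will not receive this therapy". That is hospital stay; no test is named for ICU stay or ventilator days. Kaplan-Meier, log-rank and Cox methods are given for survival and mortality only.
- *Inclusion Criteria* require ICU-level, severe or life-threatening disease.

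The article mentions no ICU-free or ventilator-free days, no composite with death, no competing-risk analysis and no restriction to survivors.

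**The concern.** A day count has a value for a patient who dies: the days until death. Taken literally, a death on ICU day 3 is a shorter, and so apparently better, stay than discharge alive on day 12. The plan itself expects about twice the mortality in controls, so the truncated counts would fall mostly in one group. Matching on age, gender, diabetes, hypertension and intubation cannot correct this, because death comes after baseline.

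The comparison of ICU stay therefore mixes three things: whether plasma shortens the stay of survivors, whether it changes the number of deaths, and how long decedents spend in the ICU before they die. The third says nothing about benefit, yet it helps to set the sign of the result. *Time of the Study* makes a larger sample and a longer trial conditional on an interim benefit, and *Interim Analysis* applies similar methods, so a misleading stay result could affect that decision.

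**Working it through.** **The plan's own figure.** A pooled two-proportion formula with 1:4 allocation, two-sided 5% and 80% power gives 115 + 460 = 575 for 12.8% vs 24.4%, a difference of 11.6 points. The printed rates, 12.4% and 24.4%, differ by 12.0 points and give 107 + 428 = 535. That mismatch is a separate matter. The printed rates are used below; with 12.8% the multiplier 0.120 becomes 0.116 and the conclusion does not change.

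**Inputs.** From *Study Population*: mortality p(CP) = 0.124, p(control) = 0.244, n = 115 and 460. Assumed, because the article does not give them: mean ICU days of survivors (S) and of decedents (D), the same in both groups, with all deaths occurring in the ICU.

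**Expected difference in means.** The mean stay in a group is p × D + (1 − p) × S. With no plasma effect on survivors' stay,

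CP − control = (0.244 − 0.124) × (S − D) = 0.12 × (S − D).

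| Decedents D (days) | Survivors S (days) | Control | CP | CP − control |
|---|---|---|---|---|
| 5 | 14 | 11.80 | 12.88 | +1.08 |
| 7 | 14 | 12.29 | 13.13 | +0.84 |
| 10 | 14 | 13.02 | 13.50 | +0.48 |
| 14 | 14 | 14.00 | 14.00 | 0.00 |
| 18 | 14 | 14.98 | 14.50 | −0.48 |
| 7 | 20 | 16.83 | 18.39 | +1.56 |

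The sign is the sign of S − D. The bias vanishes when decedents stay as long as survivors and reverses when they stay longer.

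**How often a test would react.** 2,000 simulated trials per case, 115 vs 460; survivor stay lognormal with median 10 days and log-SD 0.7; time to death lognormal with log-SD 0.7, capped at 30 days; no effect on survivors' stay; Mann-Whitney test, two-sided 5%.

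| Median day of death | Significant result on raw ICU stay |
|---|---|
| 4 | CP longer in 24%, shorter in about 0% (mean 11.8 vs 10.9 days) |
| 7 | CP longer in 7% |
| 10 | no signal (about 3% each way) |
| 14 | CP shorter in 8% |

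- If the patients whom plasma saves stay a median of 14 days, the first two rows rise to 42% and 20%.
- Harm case: plasma mortality 36.4%, deaths at median day 4. Raw stay is significantly shorter with plasma in 25% of trials.
- ICU-free days to day 30 with death scored 0 (mean 15.7 vs 13.5) favour plasma significantly in about 48% of trials, or about 30% if saved patients stay longer. They almost never point the wrong way.

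**Second model.** Gamma stays with coefficient of variation 0.6, decedents' mean 7 and survivors' mean 14 days, 3,000 trials. The CP mean is longer in 82% of trials, significantly in 17% (t test) or 20% (Mann-Whitney). With decedents at 5 days these are 90%, 24% and 31%. A true 1-day shortening among survivors (decedents 7 days) is cancelled: CP looks longer in 48% of trials and is significantly shorter in about 2%.

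**The case against.** The strongest objections concern how far the point reaches.

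- **Timing of death is unknown.** The article gives neither ICU stays nor death times, and moderate changes in these assumptions remove or reverse the bias. This stands: no single size or direction can be claimed.
- **The endpoint is not useless.** A reader might infer that no ICU-stay result, positive or negative, could be interpreted. The figures do not support that. In 1,000 simulated trials per case with survivors' stay shortened by 20% and the planned mortality benefit, raw stay was significantly shorter in 22%, 55% and 73% of trials for deaths at median day 4, 7 and 10, and never significantly longer. Raw stay loses power and can mislead when deaths are early, but it still carries information.
- **No test is fixed for ICU stay.** A reader might infer that the plan commits ICU stay to two-sample tests. The article names them for hospital stay only. They are the natural reading for another day count, but not a stated one.
- **The article is condensed.** A full protocol or analysis plan may say how death is handled. That is possible, but the endpoint variable is a protocol decision and the article states it as length of stay. Moving to ICU-free days redefines it.
- **Mortality is reported separately**, with its own models, and it drives the sample size. A shorter stay with more deaths would be seen beside those deaths. This helps a reader but does not repair the primary comparison.

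**Conclusion.** The point holds in a limited form. The only non-safety primary endpoint, and one secondary endpoint, are raw counts that death truncates, in a trial planned around 12.4% vs 24.4% mortality, and the article gives no rule for death. With no effect on survivors' stay, the shift in the mean is 0.12 × (S − D): from +1.56 to −0.48 days over the values tried. The chance of a significant result in the wrong direction runs from about 24% (deaths at median day 4) through 7% (day 7) to none beyond chance (day 10), with a reversal at day 14. These sizes rest on assumed stays and death times, on deaths occurring in the ICU, and on a two-sample test being used. What follows from the article alone is that the sign of the ICU-stay result depends partly on when patients die, and that an endpoint that avoids this is available.

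**What to change.** In *Study Endpoint and Outcome Measures*:

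1. Replace ICU length of stay with days alive and out of the ICU (or designated critical area) to day 30, and ventilator days with ventilator-free days to day 30. Give death by day 30 the worst rank in both.
2. Define one time zero for recipients and controls, for example ICU admission or the matched eligibility date. Infusion day will not serve: *Data Collection* makes it day 0, but controls have none. *Statistical Analysis* counts survival from diagnosis. If time zero precedes infusion, the analysis must account for the wait, since recipients have to survive it.
3. Compare groups by a rank or proportional-odds analysis, and name it for these endpoints.
4. Show 30-day mortality beside the result, with raw stay split by survivors and non-survivors as description only.
5. Because recruitment is under way and an interim report on 40 recipients is planned, make the change by a dated amendment before anyone sees outcomes by group.

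**Cost.** An amendment and revised wording. Days of intubation and 30-day death are already study data. *Data Collection* refers to the day of ICU admission but does not name an ICU discharge date, so the forms should be checked for it. The downside is that the endpoint mixes death and stay, so both components must always be shown with it.

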**Methods:**

Eligible patients with COVID-19 will be recruited for CP infusion according to the inclusion criteria. As COVID-19 has proven to be a moving target as far as its management is concerned, we will use current definitions according to the Ministry of Health (MOH) guidelines for diagnosis, treatment, and recovery. All CP recipients will receive supportive management including all available recommended therapies according to the available MOH guidelines. Eligible CP donors will be patients with COVID-19 who have fully recovered from their disease according to MOH recovery criteria as detailed in the inclusion criteria. CP donors have to qualify as blood donors according to MOH regulations except for the history of COVID-19 in the recent past. We will also test the CP donors for the presence of SARS-CoV-2 antibodies by a rapid test, and aliquots will be archived for future antibody titration. Due to the perceived benefit of CP, randomization was not considered. However, we will compare the outcome of the cohort treated with CP with those who did not receive CP due to a lack of consent or lack of availability. In this national collaborative study, there is a likelihood of not finding exactly matched control group patients. Hence, we plan to perform a propensity score matching of the CP recipients with the comparator group patients for the major characteristics. We plan to collect demographic, clinical, and laboratory characteristics of both groups and compare the outcomes. A total sample size of 575 patients, 115 CP recipients and 460 matched controls (1:4 ratio), will be sufficient to detect a clinically important hospital stay and 30-day mortality difference between the two groups with 80% power and a 5% level of significance.

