### Response Assessment

The response assessment includes daily clinical assessment by a physician; vital signs including temperature, blood pressure, respiratory rate, and heart rate; oxygen saturation; oxygen requirement; ventilator requirement and the modes employed; inotrope medications requirement; CBCs, liver function tests, urea, creatinine, and electrolytes daily; Apache score; Sequential Organ Failure Assessment score; fluid balance; x-ray or CT changes, repeated every 3-5 days; organs functions assessment; plasma doses and frequency requirement; transfusion-related side effects including TRALI, TACO, etc; and the SARS-CoV-2 RNA will be tested on recovery (or deterioration to determine alternative etiology).

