## Discussion

The study of the Saudi population at risk of severe COVID-19 has some distinct features, as Saudi Arabia was recently challenged by related coronaviruses including MERS-CoV that might lead to distinct immunological responses to SARS-CoV-2. The intention overriding the scientific merit of a randomized controlled trial during this pandemic is an attempt to add CP in the armamentarium against COVID-19, as this readily available agent has historically shown benefit in the treatment of related coronaviruses. There are multiple theoretical and scientific reasons to support our thinking that CP may turn out to be an effective treatment. However, the bottom line is that we do not have enough data to be certain. CP trials that have been published so far have limitations and conflicting data. Our group and others are working hard during this time to establish evidence that could support the therapeutic use of CP for patients with COVID-19.

Limitations of our study include, first, the design of the study, as we could not find it feasible to make the study a randomized controlled trial with our patient population due to the strong perceived benefit of CP in the minds of the patients and treating physicians in this situation. Second, our collaborating centers are of various levels from secondary to tertiary care hospitals with limitation of experience uniformity in conducting such a collaborative study. However, we intend to be a mutually supportive group and keep our study elements uniform. In addition, currently, anti–SARS-CoV-2 antibodies titration facilities are not available countrywide in Saudi Arabia. However, we plan to save aliquots of collected convalescent plasmas to test antibody titers whenever such facilities will be available. Last, we could not include the investigation of some biomarkers like interleukin-6 during treatment in our protocol, due to nonavailability in some centers. Nonetheless, treatment with CP seems promising to treat patients with COVID-19, and a national clinical trial to explore the efficacy and safety of CP is justified.

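### The only primary efficacy endpoint, ICU length of stay, ends at death or at a bed decision by staff who know who had plasma, so it needs a pre-specified companion measure that depends less on bed decisions and does not count early death as a short stay

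*Protocol article*

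**What the plan says.** Study Endpoint and Outcome Measures names as the first primary endpoint "ICU (or designated area for critical patients) length of stay". The other primary items are safety and the reporting of serious adverse events, so ICU stay carries efficacy alone. The secondary endpoints are days on mechanical ventilation, 30-day mortality and "days to clinical recovery as defined by the MOH". Recovery is tied to an outside definition. The article gives no criterion for the end of an ICU stay.

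On the design, the abstract says: "Due to the perceived benefit of CP, randomization was not considered". Controls are "patients who are either not consenting to receive CP or those who will not be able to receive CP due to nonavailability" (Study Population). No sham infusion or blinded assessor is described, and under Response Assessment, "The response assessment includes daily clinical assessment by a physician". The article never uses the word blinding. That staff know who had plasma is an inference from the design, though a safe one.

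The Discussion gives the reason a randomised trial was not feasible: "due to the strong perceived benefit of CP in the minds of the patients and treating physicians in this situation".

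Data Collection lists ventilation, days of intubation and nasal oxygen for all enrolled patients, and says forms exist for controls as well as recipients. Response Assessment adds "ventilator requirement and the modes employed; inotrope medications requirement", but Transfusion of CP introduces that section as the follow-up of infused patients.

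**The concern.** Two events end an ICU stay, and neither is a clean measure of recovery.

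The first is transfer out. Staff who know the treatment decide this, and the sponsor itself records that treating physicians strongly expect plasma to work. If that expectation moves the day of transfer, recipients and controls will differ in ICU stay with no biological effect. The planned matching uses age, gender, diabetes, hypertension and intubation. A transfer habit acts after treatment, so balance on these variables does not remove it.

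The second is death. In a plain count of days, a patient who dies on day 3 contributes a shorter, and so apparently better, stay than one who recovers and leaves on day 10. The same holds for a plain count of ventilation days.

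What is at stake is how the main efficacy result is read. Under Time of the Study, an interim analysis that shows benefit leads to a larger sample and a longer trial, so a distorted difference could also steer the study.

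**Working it through.** **The plan's own figure.** The 115 and 460 come from 30-day mortality, not ICU stay. For a two-sided 5% test with 80% power, 1:4 allocation and pooled variance:

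n1 = [1.96·√(p̄(1−p̄)·1.25) + 0.842·√(p1(1−p1) + p2(1−p2)/4)]² / (p2−p1)², with p̄ = (p1 + 4·p2)/5.

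- With p2 = 24.4% and the stated difference of 11.6 points (p1 = 12.8%), n1 = 114.9, so 115 + 460 = 575. This reproduces the plan.
- With the printed 12.4% and 24.4%, whose difference is 12.0 points, n1 = 106.6, so 107 + 428 = 535. That mismatch is a separate matter. Below I use 115 and 460 as stated.

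The article gives no SD, effect size or power for ICU stay, so there is no figure for that endpoint to reproduce.

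**Illustration for ICU stay.** Inputs:

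- Group sizes 115 and 460, two-sided 5% (Study Population; Statistical Analysis).
- SD of ICU stay: assumed 8 days, range 6 to 10.
- True effect: zero.
- d: the average number of days by which recipients leave earlier for reasons other than recovery. Assumed.

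Formulas:

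SE = SD·√(1/115 + 1/460) = SD × 0.1043, which gives 0.626, 0.834 and 1.043 days for SD 6, 8 and 10.

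Chance of a significant false benefit = Φ(d/SE − 1.96).

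At SD 8 and d = 1: 1/0.834 = 1.199, and Φ(1.199 − 1.96) = Φ(−0.761) = 0.223.

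| Average shift d | SD 6 | SD 8 | SD 10 |
|---|---|---|---|
| 0 | 2.5% | 2.5% | 2.5% |
| 0.5 day | 12% | 9% | 7% |
| 1 day | 36% | 22% | 16% |
| 2 days | 89% | 67% | 48% |

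If recipients are held longer by d days, the same figures give the chance of a false harm. The same shift then works against detecting a real benefit.

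**Allowing for death.** The shift d is an average over all recipients, and stays that end in death are not shifted. Suppose 24.4% of stays end that way (the planned control mortality, since no true effect is assumed). A one-day habit among the rest then averages 1 × (1 − 0.244) = 0.756 day. At SD 8, Φ(0.756/0.834 − 1.96) = Φ(−1.054) = 15%, instead of 22%.

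**Skewed stays.** The normal formula is a simplification. Simulated lognormal stays with an SD of about 10 days (median 8 or 10), compared by Mann-Whitney over 3,000 runs, gave a false benefit in 33 to 40% of trials at one day and 84 to 89% at two days. With no shift the figure was about 2%. The corresponding formula values at SD 10 are 16% and 48%, so for stays of this shape the table understates the risk.

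**Interim, 40 versus 40.** At SD 8 to 10 the false-benefit chance is about 7 to 8% at one day and 14 to 20% at two days.

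**The case against.** Much can be said for the plan.

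- **Not every stay ends with a bed decision.** Death ends some of them, and the plan itself assumes 12.4% and 24.4% mortality by day 30. This stands. It dilutes the effect of a transfer habit, as shown above, but adds the separate fault that early death counts as a short stay.
- **The direction is not known.** Recipients may have up to five daily infusions with monitoring, which could keep them in a critical-care area longer. This stands, and the point is therefore worded for either direction.
- **Other endpoints guard against misreading.** Ventilation days and 30-day mortality are already secondary endpoints, and mortality has the fullest analysis. This stands in part: mortality is not open to bed decisions, but a plain count of ventilation days is shortened by death, and nothing says how a shorter stay is to be read if the other endpoints disagree.
- **Counting a designated critical area as ICU stay may reduce dependence on bed labels.** This is fair. The article does not show that bed policy differs between recipients and controls at the same hospital, so I rest nothing on it.
- **The full protocol may hold transfer criteria.** It may, and their absence from the article is no finding. Such criteria would narrow the discretion, but unblinded staff would still apply them.
- **Support decisions are discretionary too.** Weaning and oxygen settings are made by the same staff. This stands: the remedy reduces the bias without removing it.

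A reader might infer that a small habit of early discharge is enough to manufacture a benefit. The figures do not support that. Half a day raises the false-benefit chance only to about 7 to 12%. The large figures need a systematic shift of one to two days averaged over all recipients, and nothing in the documents says that such a shift occurs.

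**Conclusion.** The point holds as a weakness in how the primary efficacy result can be read. ICU stay is the sole primary efficacy measure, treatment is known to those who decide transfers, the sponsor records their strong belief in plasma, and baseline matching cannot correct what happens after treatment. Part of any difference in stay could be transfer habit, in either direction, or early death.

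The size is illustrative. With an assumed SD of 8 days and no true effect, the chance of a significant false benefit rises from 2.5% to about 9% for a half-day average shift, 22% for one day and 67% for two. Both the SD and the shift are assumptions, and the normal formula ignores skewness.

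The documents do not show that biased transfer will occur, that it would favour plasma, or that ICU stay depends on physician discretion alone. They show that the endpoint is open to it and that the article names no measure to check it that also handles death properly.

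**What to change.** Keep ICU stay as an endpoint and add to the protocol:

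1. The same matched comparison on days alive and free of mechanical ventilation and oxygen support to day 30, counted from a start defined alike in both groups, with death given the worst value.
2. Its source: the ventilation and oxygen items in Data Collection, abstracted the same way for recipients and controls. Inotropes can be added if they are abstracted for controls too.
3. A reading rule: report this measure beside ICU stay, and state that a shorter ICU stay without support from this measure and from 30-day mortality will not be interpreted as evidence of efficacy.

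The cost is a short protocol addition, somewhat more record abstraction (mainly day-by-day support status for controls) and a more cautious claim if the measures disagree.
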